## Abstract

**Objective**: Functional dyspepsia (FD) is frequently treated in Korean Medicine (KM) clinics in South Korea. With the recent inclusion of herbal decoctions (HDs) for FD in the national pilot program for health insurance coverage, the generation of real-world evidence has become an important policy priority. In this study, we aim to evaluate the real-world clinical outcomes and safety of individualized HD-centered KM care in patients with FD in a primary care setting. **Methods**: This multicenter, prospective, single-arm observational cohort study will enroll 150 participants who meet the Rome IV criteria for FD across 23 KM clinics nationwide. Participants will receive individualized HDs, prescribed at the discretion of the attending physicians, as the primary treatment for 4 weeks. Concomitant KM treatments (e.g., acupuncture, moxibustion, and cupping) are permitted as clinically needed to preserve the pragmatic nature of routine care. The primary outcome is the change in the total symptom score on the Nepean Dyspepsia Index, Korean version (NDI-K), at week 4. Secondary outcomes include the Numeric Rating Scale for overall severity, overall treatment effect, and safety monitoring. Statistical analyses will be performed using mixed models for repeated measures to account for repeated observations and missing data. **Discussion**: This study will evaluate the pragmatic outcomes of individualized HD-centered KM care in routine clinical practice, thereby supporting the external validity of its findings. The findings are expected to provide foundational real-world data for the national HD pilot program, and these data may serve as a reference for healthcare policies and clinical decision-making. Clinical Trial Registration: Clinical Research Information Service (registration number KCT0010254); registered on 11 February 2025.

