#### 2.5.1. Primary Outcome Measure

The primary outcome is the change in the total symptom score of the Korean version of the Nepean Dyspepsia Index (NDI-K) from baseline to week 4. The NDI-K is a validated tool for quantifying the severity of dyspeptic symptoms and their impact on patient well-being. This study will use a 15-item symptom subscale that captures the frequency and intensity of discomfort; higher cumulative values represent a greater symptom burden [13]. As the original NDI comprises distinct symptom and quality-of-life subscales, this study specifically uses the 15-item Nepean Dyspepsia Symptom Index (NDSI) as the primary outcome measure to precisely evaluate core physical discomforts associated with FD, independent of general quality-of-life domains. In accordance with established clinical trial standards employing the NDSI [14], therapeutic efficacy will be evaluated primarily through continuous score reductions in this symptom subscale.

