### 2.9. Sample Size

This exploratory multicenter observational cohort study will be conducted under routine clinical conditions. Because of the lack of prior data on NDI-K changes in this specific clinical context, a formal power calculation was not performed. Instead, the target sample size was determined based on the design of previous clinical trials for HMs in FD [16] and recruitment feasibility across 23 participating KM clinics.

The dropout rate was conservatively set at 25%. Although previous multicenter clinical trials on FD in KM typically assumed a 20% attrition rate [17], a higher threshold is adopted to reflect the pragmatic nature of this study. Assuming a 25% dropout rate, recruiting 150 participants will yield approximately 112 evaluable participants, ensuring our goal of securing at least 100 fully evaluable cases for the final analysis. Furthermore, based on prior literature in which the standard deviation (SD) of NDI-K score changes was approximately 10–12 points [16], a sample of 112 evaluable participants provides high statistical precision. The expected margin of error for the mean primary outcome change is approximately 1.85–2.22 points at the 95% confidence level, providing reliable parameter estimates for this exploratory study.

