### 2.10. Statistical Analysis

Statistical significance will be set at *p* < 0.05. Baseline characteristics will be reported using mean ± SD for continuous data, while categorical data will be summarized as frequencies and percentages.

To assess clinical effectiveness, longitudinal changes in NDI-K and NRS scores across time points will be modeled using MMRM. Specifically, for the primary outcome (change in NDI-K score at week 4), the MMRM will fit categorical visit (weeks 2 and 4), baseline NDI-K score as a continuous covariate, and a visit-by-baseline interaction as fixed effects. The inclusion of week 2 data allows utilization of all longitudinal observations to stabilize covariance estimation and provide unbiased estimates of week 4 changes. An unstructured variance-covariance matrix (or a heterogeneous first-order autoregressive structure [ARH(1)] if the model does not converge) will be applied.

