To account for clinic-level clustering and intra-center correlations across the 23 participating clinics, participating sites will be included as a random effect in the mixed models. Furthermore, to accommodate potential confounding factors and treatment heterogeneity in routine clinical practice—such as baseline clinical characteristics, symptom severity, and concomitant KM interventions—multivariable regression models incorporating these key variables as covariates will be performed. Additionally, exploratory subgroup analyses based on these clinical factors may be conducted to evaluate their potential modifying effects. This approach effectively addresses within-subject correlations and handles missing data under the missing-at-random (MAR) assumption; consequently, no explicit data imputation is performed in the primary model. To test the robustness of the primary outcomes against potential departures from the MAR assumption (e.g., missing not at random), sensitivity analyses will be conducted using multiple imputation (MI) under MAR and pattern mixture models (PMMs) with delta-adjustment. Sensitivity analyses will also be conducted using the per-protocol set (PPS) to verify that the missing data pattern does not substantially alter the main findings. Additionally, paired *t*-tests will be performed as a supplementary analysis to evaluate overall within-subject pre- and post-treatment changes. Furthermore, potential assessment mode differences (in-person vs. telephone follow-up) will be evaluated by including assessment mode as a covariate or subgroup factor in secondary analytic models.

Safety monitoring data will be descriptively summarized, focusing on the frequency, intensity, and causal relationships of any recorded AEs. Exploratory subgroup analyses will also be performed based on whether participants received concomitant KM interventions. Where applicable, differences in the AE incidence rates between these subgroups will be evaluated using the chi-square test or Fisher’s exact test.

The full analysis set (FAS) will serve as the primary population for effectiveness outcomes, whereas the PPS and safety analysis set (SAS) will be used for per-protocol and safety evaluations, respectively. The specific criteria for these sets of analyses are outlined below.

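### A single-arm study of change from baseline cannot evaluate effect modification; severity subgroups also carry regression to the mean

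*Protocol article*

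**What the plan says.** The Abstract fixes the design: "This multicenter, prospective, single-arm observational cohort study will enroll 150 participants who meet the Rome IV criteria for FD across 23 KM clinics nationwide". Under section 2.5.1 the primary outcome is the change in the NDI-K total symptom score between baseline and week 4.

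Section 2.10 specifies the primary MMRM with "baseline NDI-K score as a continuous covariate, and a visit-by-baseline interaction as fixed effects". It then plans multivariable models for sources of confounding and heterogeneity, "such as baseline clinical characteristics, symptom severity, and concomitant KM interventions", and adds that "exploratory subgroup analyses based on these clinical factors may be conducted to evaluate their potential modifying effects". The same section sets the general criterion: "Statistical significance will be set at *p* < 0.05".

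The article does not say how severity would be defined or cut for these subgroups, which test would be used, or whether baseline NDI-K stays in the subgroup models. The limitations in the Introduction and section 3 name confounding, selection, reporting and expectation bias, and they rule out causal conclusions. Regression to the mean is not mentioned anywhere.

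**The concern.** An effect modifier is a factor across whose levels the treatment effect differs. To see that, one needs a treatment effect within each level, which means a comparator. Here each level supplies only a mean change, made up of natural course, expectation, regression to the mean and whatever the care adds. A difference in mean change between levels can come from any of these. For concomitant interventions chosen by the physician, it also reflects the reasons for choosing them.

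Severity is the worst case because the baseline score is itself part of the change score. Patients who score high on the day tend to score lower later, whether or not care works better for them, and there is no control arm from which to subtract that drift. The article intends its results to inform an insurance pilot programme. A statement that severe patients gain more could therefore be taken up as a finding about whom to treat, when fluctuation alone could have produced it.

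**Working it through.** **Inputs from section 2.9.** "the standard deviation (SD) of NDI-K score changes was approximately 10–12 points"; "Assuming a 25% dropout rate, recruiting 150 participants will yield approximately 112 evaluable participants".

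**The plan's own figures reproduce.** 150 × 0.75 = 112.5. The 95% margin for the mean change is 1.96 × 10/√112 = 1.85 and 1.96 × 12/√112 = 2.22.

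**Assumptions not in the documents.** These are the baseline to week-4 correlation ρ (0.5 to 0.9 shown), the ratio k of week-4 SD to baseline SD (1 unless stated), normal scores, a two-sided 5% test, and severity defined as above or below the median baseline NDI-K. No modification is built in: expected change differs between patients only through regression to the mean.

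**Formulas.** Let s₀ be the baseline SD.
- SD of change = s₀√(1 + k² − 2kρ). With k = 1, s₀ = SD of change/√(2(1 − ρ)).
- Slope of change on baseline = kρ − 1. With k = 1 this is −(1 − ρ), and the correlation of change with baseline is −√((1 − ρ)/2).
- Expected difference in change, upper minus lower half = −2√(2/π)(1 − ρ)s₀ ≈ −1.596(1 − ρ)s₀.

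Example at ρ = 0.7 and SD of change 10: s₀ = 10/√0.6 = 12.91, and the difference is −1.596 × 0.3 × 12.91 = −6.2 points.

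**Results with k = 1, n = 112.** The last two columns are simulated false-positive rates in the direction of sicker patients improving more (3,000 runs per setting).

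| ρ | correlation of change with baseline | spurious extra improvement, SD of change 10 / 12 | median-split test | linear slope on baseline |
|---|---|---|---|---|
| 0.5 | −0.50 | 8.0 / 9.6 | 99% | 100% |
| 0.7 | −0.39 | 6.2 / 7.4 | 92% | 99% |
| 0.8 | −0.32 | 5.0 / 6.1 | 77% | 93% |
| 0.9 | −0.22 | 3.6 / 4.3 | 48% | 67% |

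For scale, the 95% margin for a difference between two halves of 56 is about 1.96 × 10 × √(2/56) = 3.7 points at SD 10, and 4.4 at SD 12. At ρ = 0.9 the artefact is about as large as that margin, which fits a rejection rate near one half.

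**When the rate changes.**
- Week-4 spread (median split): k = 1.2 gives 88% at ρ = 0.5 and 33% at ρ = 0.7; k = 1.4 gives 51% and 4%. The last is near nominal because kρ − 1 = 1.4 × 0.7 − 1 = −0.02. With k = 0.8 the rate is 100% at both correlations.
- Severity split on baseline NRS, assumed to correlate 0.4 to 0.8 with baseline NDI-K and to relate to week 4 only through it: 40% to 94% at ρ = 0.5, and 25% to 76% at ρ = 0.7.
- Baseline NDI-K kept as a covariate: a two-sided test of the added severity-group term rejects in about 4% to 6% of runs. The baseline slope in that model is still kρ − 1, so it still carries the artefact.

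**The case against.** The strongest reply is that the analysis simulated above is not the one written down. The subgroup analyses are optional and exploratory. The only effectiveness model specified in detail already contains baseline NDI-K, and if the subgroup models keep it, the severity-group term behaves nominally. Severity definition, cut-point and model are details that an article may leave to a fuller document. Causality is disclaimed, and the output is called hypothesis-generating.

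Much of this stands. A reader might infer that the study will almost always report greater benefit in sicker patients. The documents do not support that: they give no correlation, SD ratio, severity definition or subgroup model, and the false-positive rate runs from near nominal to near 100% depending on them. A reader might also infer that the visit-by-baseline term in the primary model is a fault. It is not. It is an ordinary adjustment term, and nothing in the article says it will be read as effect modification.

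What does not stand is that these points rescue the stated aim. No fuller plan can supply a comparator to a single-arm study. The exploratory label lowers the weight of a result but does not remove a bias of known source. The causal disclaimer sits badly beside the aim, because an effect that is not identified cannot have its modification identified. Baseline adjustment protects the added group term; it does not turn the slope on baseline, or any subgroup difference, into a modifying effect.

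**Conclusion.** The point holds for the stated purpose of the subgroup analyses. Effect modification is not estimable in this design for any of the listed factors, and that conclusion needs no assumption beyond the single arm and the change-from-baseline outcome.

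The size of the severity artefact is conditional. For an unadjusted median split on baseline NDI-K with similar SDs and n = 112, the false-positive rate is about 48% to 99% over assumed correlations of 0.9 down to 0.5, with a spurious difference of roughly 3.6 to 9.6 points. It is smaller under the conditions listed in the check, and about 5% for a severity-group term with baseline NDI-K retained. No figure stated in the article is wrong, and the primary week-4 estimate is untouched. This is a correction to the wording and interpretation of a secondary, optional analysis, worth making because the results are meant to inform coverage policy.

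**What to change.** In section 2.10, replace the clause about modifying effects with wording such as: *to describe change by subgroup; a single-arm study cannot separate effect modification from prognosis or regression to the mean*. In addition:

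- keep baseline NDI-K as a covariate in every subgroup model;
- show baseline and week-4 scores by severity group descriptively;
- state that neither the baseline slope nor a severity-group difference will be interpreted as effect modification.

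Do not substitute a test of change against the average of the two scores (Oldham, equivalent to the Pitman-Morgan comparison of variances). It tests equality of the two variances and is biased when response varies between patients or when scores reach a floor. With response variation unrelated to severity, at an assumed 25% of the baseline variance, it rejects in roughly a quarter to a half of runs at n = 112 over correlations of 0.5 to 0.9.

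The cost is a few sentences and one covariate already collected, while recruitment is still open. The price is that no effect-modifier claim can be made from these subgroups.

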### 2.4. Interventions

Because this is an observational study, no experimental intervention is assigned or controlled by the researchers. During the 4-week observation period, participants will receive individualized KM treatments, defined as “HD-centered care,” in which tailored HDs serve as the primary therapeutic modality, supplemented by routine individualized KM care as dictated by the attending physician.

Although HDs are flexibly individualized based on pattern identification, representative formulas frequently prescribed in primary care for FD include Banha-sasim-tang, Yukgunja-tang, and Hyangsa-pyeongwi-san [8,9,12]. These traditional formulas are well documented for improving gastrointestinal motility, modulating visceral hypersensitivity, and protecting the mucosal barrier through key bioactive compounds, and they have a well-established safety profile in clinical practice.

In principle, HDs are prescribed in standard dispensing units (typically comprising 20 therapeutic doses yielding 30 packs, designated for administration three times daily), though these may be adjusted according to individual clinical conditions and practice environments. Detailed prescriptions and dosage information—including repeated prescriptions—will be recorded, and patient adherence to HDs will be monitored based on patient-reported remaining pack counts during follow-up assessments.

Other KM treatments administered as part of routine care, such as herbal extract granules, acupuncture, electroacupuncture, moxibustion, cupping therapy, and pharmacopuncture, may also be provided at the treating physician’s discretion. Detailed information on all KM interventions and concomitant medications, including prescription duration, administration frequency, and concomitant treatments, will be thoroughly documented in the electronic case report form (eCRF) to capture treatment exposure and heterogeneity.

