### 2.5. Outcome Measures

Clinical assessments are scheduled at baseline (week 0), week 2, and week 4. For participants who are unable to visit the clinic in person at week 2 or 4, assessments may be conducted via telephone interviews to minimize missing data and ensure continuity. Missing outcome data will not be imputed and will be managed within the mixed models for repeated measures (MMRMs).

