#### 2.6.3. Treatment and Follow-Up Visits

Participants will return for follow-up evaluations at weeks 2 and 4. These visits involve updating the NDI-K and NRS scores, reviewing changes in herbal prescriptions, and documenting concomitant therapies or adverse events to track the longitudinal impact of treatment. Patient adherence to HDs will be systematically assessed at each follow-up visit based on patient-reported counts of remaining pouches. Unscheduled visits, defined as visits occurring when participants present to the clinic outside of scheduled visit time points, will also be documented to capture all relevant clinical data.

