### 2.7. Safety Assessment

Adverse events (AEs) will be monitored at each visit. All AEs will be recorded in detail, including the onset, duration, severity, outcome, and management. AEs will be categorized using version 5.0 of the Common Terminology Criteria for Adverse Events (CTCAE). The causal relationship between AEs and HDs will be assessed independently by the investigators based on their clinical judgment. If necessary, external expert consultation may be sought to confirm the causality assessment. All AEs will be managed with appropriate clinical care until resolution. Any serious adverse event (SAE) must be reported to the Principal Investigator and IRB within 24 h of awareness. As this study reflects routine primary care practice, protocol-mandated laboratory safety tests will not be routinely collected.

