**ASSESSMENTS:**					
Overall treatment effect			X	X	
Numeric Rating Scale		X	X	X	
Nepean Dyspepsia Index-Korean		X	X	X	
Korean medicine treatment record		X	X	X	X
Concomitant medication		X	X	X	X
Adverse events		X	X	X	X

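### AE incidence is to be tested between patients with and without add-on KM treatment, although add-on patients may be asked about AEs more often; the size of the resulting bias is unknown

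*Protocol article*

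**What the plan says.** Section 2.7 states that "Adverse events (AEs) will be monitored at each visit". In Table 2 the row "Adverse events" is marked at Visits 1, 2 and 3 and also in the unscheduled-visit column; the KM treatment record is marked in the same four columns. Section 2.6.3 reads: "Unscheduled visits, defined as visits occurring when participants present to the clinic outside of scheduled visit time points, will also be documented". No limit on their number is given.

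Section 2.4 lists the add-on treatments: "such as herbal extract granules, acupuncture, electroacupuncture, moxibustion, cupping therapy, and pharmacopuncture, may also be provided at the treating physician’s discretion". Section 2.5 allows weeks 2 and 4 to be done remotely: "assessments may be conducted via telephone interviews to minimize missing data and ensure continuity".

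Section 2.10 forms subgroups by whether concomitant KM treatment was received and says that "differences in the AE incidence rates between these subgroups will be evaluated using the chi-square test" or Fisher's exact test, where applicable. It does not limit this comparison to scheduled contacts, use a rate per contact or adjust for the number of contacts. The covariate models and the assessment-mode analysis in the same section are described for effectiveness and are not tied to the AE comparison.

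**The concern.** The variable that defines the two groups can also determine how often each group is asked about AEs. All the listed add-ons except the granules are normally given in person. A session away from weeks 0, 2 and 4 meets the definition of an unscheduled visit, at which AEs are collected. A patient on HD alone may have as few as two post-baseline inquiries, possibly both by telephone.

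Mild, short-lived events are more likely to be recorded when the question comes soon after them. The add-on group can therefore show a higher AE percentage with no true difference, and HD-only care can look safer than it is. This is unequal ascertainment and not confounding: it would remain if add-ons were assigned at random and were harmless, and covariate adjustment would not remove it. The limitations in the Discussion name the missing control group, heterogeneity, and reporting and expectation bias, but not this. Safety is one of the study's two stated aims, so the displayed percentages matter as well as the p-value.

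**Working it through.** **The plan's own figure.** The article gives no figure for the AE comparison. Its one computed figure, the margin of error in section 2.9, reproduces (1.96 × 10/√112 = 1.85; 1.96 × 12/√112 = 2.22) but does not bear on this point.

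**Inputs from the article.** Observation over 4 weeks (28 days); scheduled inquiries at weeks 2 and 4; a typical dispensing unit of 30 packs taken three times daily, so 30/3 = 10 days' supply (section 2.4); p < 0.05 (section 2.10); at most 150 participants in the safety set.

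**Assumptions, not in the article.** Equal true AE risk in both groups; onset uniform over 28 days; the chance that an AE is reported halves every h days until the next inquiry, with h = 7 or 14; true incidence 30% or 10%; HD-only v add-on group sizes of 50 v 100, 100 v 50 and 75 v 75.

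**Step 1: detection.** With λ = ln 2/h and gaps g between inquiries, the proportion of AEs detected is D = Σ(1 − 2^(−g/h)) / (28λ). The denominator is 4 ln 2 = 2.773 for h = 7 and 2 ln 2 = 1.386 for h = 14. For inquiries at days 14 and 28 with h = 7, D = 2 × (1 − 0.25)/2.773 = 0.541.

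| Inquiry days | h = 7 | h = 14 |
|---|---|---|
| 14, 28 (HD-only, scheduled contacts only) | 0.541 | 0.721 |
| 10, 14, 20, 28 (HD-only, in-person refills) | 0.704 | 0.833 |
| every 7 (add-on, weekly) | 0.721 | 0.845 |
| every 3.5 (add-on, twice weekly) | 0.845 | 0.918 |

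**Step 2: spurious AE ratio** = D(add-on)/D(HD-only). For example, 0.845/0.541 = 1.56 and 0.845/0.833 = 1.015. The ratio does not depend on the true incidence.

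**Step 3: rejection rate.** Recorded incidence is the true incidence × D in each group. The rejection rate of the uncorrected two-sided chi-square test at 0.05 comes from exact binomial enumeration. Ranges cover both half-lives and all three splits.

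| HD-only inquiries | Add-on sessions | Spurious ratio | Rejects, 30% incidence | Rejects, 10% incidence |
|---|---|---|---|---|
| 14, 28 | weekly | 1.17–1.33 | 8–14% | 5–8% |
| 14, 28 | twice weekly | 1.27–1.56 | 12–28% | 5–12% |
| 10, 14, 20, 28 | weekly | 1.02–1.03 | about 5% | 4–5% |
| 10, 14, 20, 28 | twice weekly | 1.10–1.20 | 6–10% | 5–7% |

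With the same inquiry schedule in both groups D is equal, the ratio is 1, and the test rejects in about 5% of trials or fewer.

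**The case against.** The strongest reply is that nothing in the article shows a large imbalance.

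- **HD-only contacts.** A reader might infer that HD-only patients have exactly two post-baseline inquiries. The article does not support that. A typical unit lasts 10 days, and section 2.4 provides for recording repeated prescriptions. If units are dispensed one at a time and collected in person, refills fall near days 10 and 20, and such attendances outside the scheduled time points are unscheduled visits with AE collection. Against weekly sessions this removes nearly all of the bias. If several units are dispensed at once or delivered, the bias returns. The article does not settle which applies.
- **Add-on contacts.** That add-ons bring patients in more often is an inference. No session frequency is stated, add-ons may be given at the scheduled visits, and granules need no session. The ±7-day windows in Table 2 run without a gap from day 7 to day 35, so it is unclear which sessions would be logged as unscheduled.
- **Recall.** Section 2.7 has onset and duration recorded, so scheduled contacts are meant to pick up past events. For this reason a model that gives each inquiry its own independent chance of yielding an AE is too harsh, and the result does not rest on it. The half-lives used here are themselves assumed.
- **Status of the comparison.** It is exploratory, and the safety analysis is otherwise descriptive. A reader might infer that this contrast is meant to inform the insurance pilot program. The article says that only of the study as a whole, which it calls hypothesis-generating.

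All of this stands as a limit on size and certainty. The mechanism also stands: unscheduled visits count for AE collection, most add-ons need attendance, and the planned test takes no account of either.

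**Conclusion.** The concern holds as a possible ascertainment bias of unknown size. The unadjusted comparison can show more AEs in the add-on group with equal true harm, and nothing stated in section 2.10 guards against it. Under reporting half-lives of 7 to 14 days, the spurious ratio ranges from about 1.02 (HD-only patients attend for refills; weekly sessions) to 1.56 (HD-only patients asked only at weeks 2 and 4; twice-weekly sessions). The test rejects in about 5% to 28% of trials at 30% true incidence and in about 4% to 12% at 10%. At low incidence the error rate is thus only mildly inflated, but the displayed percentages are distorted by the same ratio. The documents do not support saying that the add-on group will show an excess, only that it may.

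**What to change.** In section 2.10:

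1. Report the number of AE inquiries per participant, scheduled and unscheduled, for each group beside the AE percentages.
2. Flag each AE by the type of visit at which it was captured.
3. Present the add-on v HD-only contrast descriptively, as a difference with a confidence interval in place of a significance test, and state that ascertainment may differ. The interval covers sampling error only, so this statement is needed.
4. Where feasible, as a sensitivity analysis in participants still to be enrolled, put one identical AE question to everyone at Visits 2 and 3. It should cover the whole interval since the previous scheduled visit, including events already reported. Compare the groups on that record.

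Items 1 to 3 rest largely on visits and AEs that are already documented, plus one source flag in the eCRF, and cost the p-value of one exploratory contrast. Item 4 has real limits. Recruitment has run since February 2025, so participants already followed cannot be asked. It introduces a second AE question mid-study. Patients questioned more often may also recall better, so it reduces the imbalance without removing it. Overall AE reporting is unchanged.
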